**Methods:**

This will be a prospective, single cohort, pre- and posttest study examining the effect of a brief informative video describing moral distress on perceptual, psychological, and physiological indicators of stress and decision-making during a scenario known to potentially elicit moral distress. To accomplish this, we have developed a virtual reality simulation that will be used before and after the digital intervention for monitoring short-term impacts. The simulation involves an intensive care unit setting during the COVID-19 pandemic, and participants will be placed in morally challenging situations. The participants will be engaged in an educational intervention at the individual, team, and organizational levels. During each test, data will be collected for (1) physiological measures of stress and after each test, data will be collected regarding (2) thoughts, feelings and behaviors during a morally challenging situation, and (3) perceptual estimates of psychological stress. In addition, participants will continue to be monitored for moral distress and other psychological stresses for 8 weeks through our Digital intervention/intelligence Group mobile platform. Finally, a comparison will be conducted using machine learning and biostatistical techniques to analyze the short- and long-term impacts of the virtual reality intervention.

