### Compound Intervention

The compound intervention is composed of the virtual reality simulation-based educational intervention and data collection of mental health and moral injury surveys. The virtual reality simulation-based educational intervention contains a moral injury educational video based on the Moral Injury Guide developed by the Ottawa PTSD Center for Excellence [17].

The latter component of the compound intervention evaluates the effectiveness of the virtual reality simulation-based educational intervention through mental health surveys. These surveys include the Perceived Stress Scale (PSS), Moral Injury Outcome Scale (MIOS), Igroup presence questionnaire (IPQ), and Adapted Moral Injury Symptom Scale: Health care Professionals Version (MISS-HP). PSS is a self-report instrument that evaluates level of stress. MIOS and MISS-HP are tools that evaluate the effect of moral injury, and the IPQ is a questionnaire that evaluates the experience of presence during virtual reality simulations. We will use this information to improve our compounded intervention for use on digital platforms iteratively.

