### Mobile Data Collection

#### Active Data

The surveys will pop up on fixed days of the week for active data collection (ie, Monday, Wednesday, and Friday), as reminders. The participants are then free to complete the surveys (Table 4). These surveys will allow for monitoring of stress-related symptoms using validated scales—Daily surveys using 15 items taken from the UCLA Loneliness Scale [22] (3 items), PSS [23] (4 items), Generalized Anxiety Disorder [24] scale (2 items), Patient Health Questionnaire [25] (2 items), and MIOS [26] (4 items). Each week, on the weekend, the complete versions of the PSS [23] (10 items), Generalized Anxiety Disorder [24] scale (7 items), Patient Health Questionnaire [25] (9 items), MIOS [26] (10 items). Once during the study, the App Experience Survey (6 items) will be administered.

The content of the Moral Injury Outcome Scale is more specific to reflect the virtual reality scenario, unlike in the mobile study, where the survey is more generalized. The cognitive tests appear similar to electronic games wherein participants have to complete a trail or pattern. We will collect the time and number of errors made by the participants.

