#### Passive Data

Passive data (GPS and accelerometer data) are collected automatically while the phone is on, even when the participant is not using the phone (Table 4). The app will access information collected and stored on the phone. Participants can opt out of this feature if they choose.

GPS collects data of the participant’s location data with 3-meter accuracy; however, the participant’s specific location will not be used as data in the study. The app collects GPS data constantly, and data are immediately converted into broad summary metrics, such as the distance per day and or unique locations visited. These data are not monitored in real time, and will not be reviewed by and party.

The accelerometer records triaxial acceleration, which can be used to indicate if the participant is running or walking. These data are not monitored in real time.

Participants may receive an automated alert based on established survey cut-offs at the beginning of the study. After some time, these alerts may be based on the participant’s change in scores compared to their own baseline. The alerts will be simple, for example, “your score today suggests mild anxiety, we suggest exercise, mindfulness practice, etc.” If more than 1 alert is required because more than 1 scale has reached the cut-off, the alert will be given once for all the scales.

For active data, we will use visual analog scales (Figure 10). The scale is linear and continuous for the participant to slide on. The scale is subdivided into varying Likert items according to the questionnaire (eg, a scale with 4 items).

We will use predetermined cut-offs (Table 4) to establish the score for each assessment.

Passive data (eg, GPS, accelerometer) will be collected for the first 2 weeks at the beginning of the study to establish a baseline. Members of the research team will be monitoring the in-person data collection for safety concerns. In addition, participants who are inactive will be contacted to remind them of data collection and patients who are having problems will be contact to give technical support.

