	**Perceived Stress Scale**					
		Low	0≤score<14		“Based on your scores during the past week, you do not appear to have increased stress which is mild/moderate; recommendations include Bibliotherapy, mindfulness, exercise, sleep management”	
		Moderate	14≤score<27		“Based on your scores during the past week, you do not appear to have increased stress which is mild/moderate; recommendations include Bibliotherapy, mindfulness, exercise, sleep management”	
		High	score≥27		“Based on your scores during the past 2 week, you appear clinically stressed which is severe; In addition to continued Bibliotherapy, mindfulness, exercise, sleep management”	

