**Passive data**						
	**GPS mobility metrics, call-test logs, latency of response, phone pattern of use, sleep, activity**					
		Moderate change	1 SD to 2 SD from baseline		“Based on your (specify item) scores during the last 2 weeks, you appear to have moderately increased or decreased (specify item); If increased: recommendations include continued exercise; If decreased: recommendations include Bibliotherapy and more exercise”	
		Large change	>2 SD from baseline; direction of change is important		“Based on your (specify item) scores during the last 2 weeks, you appear to have severely increased or decreased (specify item); If increased: recommendations include continued exercise; If decreased: recommendations include Bibliotherapy and more exercise. Also link provided for further help.”	

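### The 8-week course is credited to the VR intervention, although there is no control and the app gives self-help advice not listed as intervention; Table 4 also ties advice to every PSS score

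*Protocol article*

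**What the plan says.** The Abstract (Methods) describes a single-cohort pre/post study in which "participants will continue to be monitored for moral distress and other psychological stresses for 8 weeks" through the mobile app. It closes by announcing an analysis of short- and long-term effects, both credited to the VR intervention. Overview, Longitudinal Monitoring and Trial Design also present the app phase as monitoring.

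The intervention is defined under Compound Intervention: "The compound intervention is composed of the virtual reality simulation-based educational intervention and data collection of mental health and moral injury surveys". That section mentions neither alerts nor the app's own content.

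Other sections show what the app does:

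- **Platform description.** The Learn module gives health tips. The Manage module offers a diary or personalized interventions.
- **Passive Data (alert rule).** "Participants may receive an automated alert based on established survey cut-offs at the beginning of the study". The rule may later switch to each person's deviation from their own starting level. An alert is tied to a scale reaching its cut-off, and several simultaneous triggers give one alert.
- **Table 4, PSS.** Low runs from 0 to below 14, Moderate from 14 to below 27, High from 27 upward. Low and Moderate carry the same message: "you do not appear to have increased stress which is mild/moderate; recommendations include Bibliotherapy, mindfulness, exercise, sleep management".
- **Table 4, anxiety and depression scales.** The lowest band with a message starts at 5 on both.
- **Table 4, passive metrics.** A message is due at "1 SD to 2 SD from baseline" (moderate change) or beyond 2 SD (large change). Its wording refers to the last 2 weeks.
- **Active Data.** Short surveys are prompted on "Monday, Wednesday, and Friday"; the full 10-item PSS is given each weekend.

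**The concern.** A phase that is only monitoring leaves the participant's course undisturbed. This one does not. The advice (reading, mindfulness, exercise, sleep) is aimed at the same quantities that the app records, and the PSS is both an alert trigger and an outcome. Any 8-week trend is therefore the joint result of the VR session, the video, the app advice, the app content and whatever else changes over 8 weeks of a pandemic. A report that follows the Abstract would credit that trend to the VR intervention alone.

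Two points in Table 4 bear on how much advice is given. The PSS rows leave no score without a recommendation, which does not fit an alert that depends on reaching a cut-off. The passive rule is expressed in SDs without saying what is compared (a day, a week or a 2-week mean), so how often it fires with no real change cannot be read from the plan.

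**Working it through.** The plan gives no alert rate, power or effect size, so there is no figure of its own to reproduce.

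**1. Exposure during the 8 weeks.**

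| Component | Described in | Listed under Compound Intervention? |
|---|---|---|
| VR session and video | Experimental Flow | Yes |
| Survey collection | Active Data | Yes |
| Learn and Manage content | Platform description | No |
| Alerts with self-help advice | Passive Data, Table 4 | No |

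Participant Anonymity says app use starts only after the VR component. The pre/post comparison within the session is therefore complete before any alert can be sent, and the problem is confined to the 8-week phase.

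**2. PSS bands.** Assumption: ten items scored 0 to 4, so a range of 0 to 40 (the item scoring is not in the document).

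- Low, 0 to 13: 14 scores
- Moderate, 14 to 26: 13 scores
- High, 27 to 40: 14 scores

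14 + 13 + 14 = 41 of 41 possible scores carry a recommendation. By contrast, scores 0 to 4 on the anxiety and depression scales trigger nothing. With one full form a week, the ceiling is 8 PSS messages per participant, or 8 × 15 = 120 in 15 participants. On the 4-item form with the same scoring the maximum is 16, so the High band could not be reached; the bands suit the weekly full form.

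**3. Passive rule with no true change.** Inputs: a 2-week baseline, taken as 14 daily values (Passive Data), and the 1 SD threshold (Table 4). Assumptions: normal daily values, and mean and SD estimated from the 14 baseline days. The mean of w later days minus the baseline mean, divided by the baseline SD, is distributed as √(1/w + 1/14) times a t variable with 13 df. So

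P(beyond 1 SD) = P(|t₁₃| > 1/√(1/w + 1/14)).

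| Unit compared | √(1/w + 1/14) | Critical t | Chance rate per metric |
|---|---|---|---|
| Single day (w = 1) | 1.035 | 0.966 | 35.2% |
| 7-day mean | 0.463 | 2.160 | 5.0% |
| 14-day mean | 0.378 | 2.646 | 2.0% |

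These figures assume independent days. A simulation of 20,000 series of 56 days with first-order autocorrelation, using non-overlapping 14-day means, gave 2.1% at correlation 0 (agreeing with the formula), 7.8% at 0.3, 16.3% at 0.5 and 31.8% at 0.7. The document gives no autocorrelation; this range is assumed.

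**The case against.** The strongest reply has five parts.

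- **Feasibility aim.** The study sets out to show feasibility of both platforms and defers efficacy to later studies. That limits the weight of the point, but the Abstract still states a long-term analysis credited to the VR intervention, and Compound Intervention says the surveys evaluate that intervention's effectiveness.
- **No control.** A single cohort could not support long-term attribution even with the alerts switched off. This stands. The app advice is a further, specific cause, not the sole obstacle.
- **Nothing is hidden.** The modules and alerts are openly described, and survey collection is counted in the compound intervention. True, but advice and app content are not counted there.
- **The Low row may only classify.** The text also uses the cut-offs to score each assessment, and the messages are headed as examples. That is possible, but the row carries a recommendation, so the document has to say which is meant.
- **Article-level detail.** The passive time unit may be set out in a fuller document. This stands in good part, so that item is a clarification and not the core of the point.

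A reader might infer more than the text supports:

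- *That the alerts are near-continuous.* Alerts are permissive and merged, completion is voluntary, the full PSS is weekly, and the rule may later switch to change from own baseline. The 120 messages are a ceiling that needs every form completed, every message sent and no such switch.
- *That passive alerts fire largely by chance.* The only window stated for them is 2 weeks, where the rate is about 2% per metric with independent days. The sentence about today's score is a survey example and does not set a daily passive rule. Passive collection can also be declined.
- *That missing about half of true 1 SD shifts is a defect.* Any threshold set equal to the shift behaves that way.

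**Conclusion.** The point holds for the 8-week phase. The plan credits the long-term course to the VR intervention in a single cohort without a control, while the app gives advice and content on the same constructs that it measures and the definition of the intervention omits both. The course can be described only as that of the combined package. The within-session comparison is not touched.

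The PSS inconsistency is exact: every score falls in a band with a recommendation (41 of 41, on an assumed 0 to 40 range), and two differently labelled bands share a message saying stress is not increased. Which version should govern is not judged here; the passages must be reconciled.

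The passive rule is under-defined rather than shown to be faulty. Its chance rate per metric is about 2% for a 2-week mean with independent days, up to about 32% at an assumed autocorrelation of 0.7, and about 35% if evaluated daily. How many alerts will be sent cannot be derived from the document.

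**What to change.** 1. In the Abstract (Methods) and Compound Intervention, define the exposure behind the 8-week results as the VR session and video plus the app with its alerts. Replace the statement that credits long-term impact to the VR intervention with a descriptive one about this package.
2. Time-stamp every alert and report the number per participant descriptively. Do not use cumulative alerts as an adjustment covariate: alerts are triggered by the outcome, a message at every weekly PSS would make the count equal to week number, and 10 to 15 participants cannot support the model.
3. Reconcile the PSS Low row, and the message it shares with Moderate, with the alert rule under Passive Data.
4. State the time unit of the passive comparison, compute the SD on that same unit, and give the resulting chance rate. A 2-week baseline contains only one 2-week mean, so if that unit is chosen the plan must also say how its SD is obtained.

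The cost is wording and one log table from the app. The downside is a narrower claim about the VR intervention.

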	**Patient Health Questionnaire -9**					
		Mild depression	5≤score<10		“Based on your scores during the past week, you do not appear clinically anxious/depressed, which is mild/moderate; recommendations include Bibliotherapy, mindfulness, exercise, sleep management”	
		Moderate depression	10≤score<15		“Based on your scores during the past week, you do not appear clinically anxious/depressed, which is mild/moderate; recommendations include Bibliotherapy, mindfulness, exercise, sleep management”	
		Moderately severe depression	15≤score<20		“Based on your scores during the past week, you appear clinically anxious/depressed, which is severe; In addition to continued Bibliotherapy, mindfulness, exercise, sleep management”	
		Severe depression	score≥20		“Based on your scores during the past week, you appear clinically anxious/depressed, which is severe; In addition to continued Bibliotherapy, mindfulness, exercise, sleep management”	
	Cognitive test: Trails B			>3 minutes or 3 errors		“Your cognition score today is reduced, potential interventions: A) Mindfulness, B) Exercise, C) Sleep habits”
**Passive data**						
	**GPS mobility metrics, call-test logs, latency of response, phone pattern of use, sleep, activity**					
		Moderate change	1 SD to 2 SD from baseline		“Based on your (specify item) scores during the last 2 weeks, you appear to have moderately increased or decreased (specify item); If increased: recommendations include continued exercise; If decreased: recommendations include Bibliotherapy and more exercise”	
		Large change	>2 SD from baseline; direction of change is important		“Based on your (specify item) scores during the last 2 weeks, you appear to have severely increased or decreased (specify item); If increased: recommendations include continued exercise; If decreased: recommendations include Bibliotherapy and more exercise. Also link provided for further help.”	

### Mobile Data Analysis

Smartphones are ubiquitous in our daily lives and incorporate a suite of sensors, such as accelerometer and GPS. In addition, digital platforms can be used to collect active data. This results in a multimodal system on a smartphone device. To objectively analyze the data, preprocessing will include Kalman filtering, GPS data cleaning, and Wavelet transforms, and feature extraction techniques, such as multiview biclustering [27] and statistical and structural features from time-series signals [28], will be used for machine learning (decision tree, logistic regression, and support vector machine) to find associations between passive and active data. These models are simple, consume low power, and have the capability of explainable artificial intelligence to understand our machine learning models better [29]. We plan to extend the machine learning models to long short-term memory and convolutional neural networks due to the popularity and effectiveness of the models in mobile data analysis [28].

### Analysis Approach

Signals (Figure 11; Multimedia Appendix 4) will be collected with a sampling frequency of 2000 Hz. The software used to collect the data from Biopac performs all internal calculations to the accuracy defined by the IEEE format for double-precision floating-point numbers and stores the results of those calculations in double-precision floating-point format; this format assigns 8 bytes to all numbers in calculations or resulting from calculations [30]. Biopac equipment has an interface to interact with the virtual reality scenario; thus, we have markers for the sessions, such as the start and end of the session and when the user answers a question.

**Figure 11 figure11:**
[figure not shown]
Physiological signal examples: respiration impedance (RI), photoplethysmography (PPG), electrocardiogram (ECG), and galvanic skin response (GSR).

Numeric programming computing software will be used to conduct the analysis. The signals will be collected in a raw format. Preprocessing, feature extraction, and machine learning will be applied to the data. Preprocessing involves techniques such as low-pass filters, high-pass filters, and notch filters to remove noise. The filtered signal will then be passed along to extract features. Feature extraction will involve extracting attributes of the signals to be better represented. Techniques for feature extraction include handcrafted features, such as statistical values. Lastly, machine learning techniques such as decision tree, random forest, and logistic regression will be used for classification. These techniques are chosen due to their ability to manage small sample sizes. Once familiar with the newly acquired data set, we will reflect on a new approach for analysis.

## Results

As of March 20, 2021, the research ethics board at St. Michael’s Hospital has approved the study (UHTDTS25377). This project was funded on November 20, 2020.

## Discussion

As previously explored, this research will develop and validate the use of digital platforms, specifically virtual reality and mobile apps to understand the continuum of moral distress that leads to moral. Demonstration of feasibility will lead to future studies to examine the efficacy of these digital interventions.

We hypothesize that features of the physiological data will help to identify mental health disorders and distress within users. For example, many studies [31,32] have looked at the impact of stress and burnout in health care workers due to the COVID-19 pandemic.

Modern signal processing and classification tools will be used to find associations between the data and mental health surveys. We expect to discover identifiers within physiological signals that reflect distress and other psychological disorders in the short- and long-term fluctuations of the passive data response related to mental health.

Given the pilot project’s aims, the number of participants (10-15 health care providers) was chosen with a view toward demonstrating feasibility while taking into consideration the availability of participants during the COVID-19 pandemic.

Determining the feasibility and utility of virtual reality environments to aid health care workers in reducing distress and becoming resilient in morally challenging and complex environments, by using physiological data in a personalized digital phenotype profile with mobile platforms will lead to future work on the implementation of a larger scale study.

## Appendix

Multimedia Appendix 1 Requirements for LAMP (Learn, Assess, Manage, Prevent) mobile app servers.

Multimedia Appendix 2 Moral Injury Outcome Scale and Perceived Stress Scale.

Multimedia Appendix 3 Adapted Moral Injury Symptom Scale: Healthcare Professionals version.

Multimedia Appendix 4 Additional physiological signals.

## Abbreviations

IPQ: Igroup presence questionnaire
MIOS: Moral Injury Outcome Scale
MISS-HP: Moral Injury Symptom Scale: Healthcare Professional version
PSS: Perceived Stress Scale
